## Abstract

**Background:**

Missing health care appointments without canceling in advance results in a *no show*, a vacant appointment slot that cannot be offered to others. No show can be reduced by reminding patients about their appointment in advance. In this regard, mobile health (mHealth) strategy is to use text messaging (short message service, SMS), which is available on all cellular phones, including cheap low-end handsets. Nonattendance for appointments in health care results in wasted resources and disturbs the planned work schedules.

**Objectives:**

The purpose of this study is to evaluate the efficacy of the current text messaging (SMS) and call-based reminder system and further explore how to improve the attendance at the pediatric outpatient clinics. The primary objectives are to (1) determine the efficacy of the current clinic appointment reminder service at pediatric outpatient clinics at Aga Khan University Hospital, (2) assess the mobile phone access and usage among caregivers visiting pediatrics consultant clinics, and (3) explore the perception and barriers of parents regarding the current clinic appointment reminder service at the pediatric outpatient clinics at Aga Khan University Hospital.

**Methods:**

The study uses a mixed-method design that consists of 3 components: (1) retrospective study (component A) which aims to determine the efficacy of text messaging (SMS) and phone call–based reminder service on patient’s clinic attendance during January to June 2017 (N=58,517); (2) quantitative (component B) in which a baseline survey will be conducted to assess the mobile phone access and usage among parents/caregivers of children visiting pediatrics consultant clinics (n=300); and (3) qualitative (component C) includes in-depth interviews and focus group discussion with parents/caregivers of children visiting the pediatric consultancy clinic and with health care providers and administrative staff. Main constructs will be to explore perceptions and barriers related to existing clinic appointment reminder service. Ethics approval has been obtained from the Ethical Review Committee, Aga Khan University, Pakistan (4770-Ped-ERC-17).

**Results:**

Results will be disseminated to pediatric quality public health and mHealth communities through scientific meetings and through publications, nationally and internationally.

**Conclusions:**

This study will provide insight regarding efficacy of using mHealth-based reminder services for patient’s appointments in low- and middle-income countries setup. The finding of this study will be used to recommend further enhanced mHealth-based solutions to improve patient appointments and decrease no show.

## Introduction

Nonattendance for appointments in health care results in wasted resources and disturbs the planned work schedules. Missing health care appointments without canceling in advance results in a “no show,” a vacant appointment slot that cannot be offered to others. In 2015, the UK Secretary of State for Health estimated that missed general practitioner and hospital appointments cost the National Health Service an estimated £912 million per year [1], and most appointments are missed due to simple reasons such as forgetfulness [2,3].

Mobile health, or mHealth, is defined as medical and public health practices supported by mobile devices. There has been a drastic increase in the usage of mobile phones with around 7 billion mobile phone subscribers globally, 89% of whom live in developing countries [4,5]. The portability of mobile phones makes this a flexible means of communication through which people can be contacted swiftly and can respond at their own convenience. The cost-effectiveness of this technology is reflected by the fact that even a substantial proportion of those living on less than US $1 per day have access to mobile phones and their SMS text messaging (short message service, SMS) [6]. A recent analysis assessing the socioeconomic impact of telecommunication in a developing country found that people living in rural areas benefit from telecommunication even more than those living in urban areas [6]. Mobile phones have thus changed the mode of communication among people worldwide and provide a great potential for engagement in care of patients with their health care provider [7]. SMS text messaging–based interventions have been quite effective in different programs, particularly in treatment adherence, nutrition programs, antenatal care attendance, and adherence for routine pediatric immunization [8]. In addition, available data show evidence for mobile phone–based SMS text messaging reminders to improve health care appointments’ attendance and reduce “no shows” [9,10].

“No shows” can be reduced by engaging frequently with the patient, and reminding them about their appointment in advance. In this regard, one such health strategy is the use of SMS text messaging and phone calls. Various studies have shown how SMS text messaging reminders are effective for health care appointment attendance in different settings. A recent randomized controlled trial investigating the impact of SMS text messaging reminders on attendance rates at outpatient clinics in a psychiatric hospital found that receiving an SMS text messaging reminder independently reduces the chance of missing the next appointment by 50% [11]. Another study in a university setting in Switzerland found that both, SMS text messages and telephonic reminders were equally useful in reducing the number of missed appointments; however, SMS text messages were found to be more cost-effective [12]. SMS text messaging reminders at weekly intervals have also proven to be an efficacious method of improving adherence to antiretroviral therapy in patients with HIV [13]. Wang et al reported clinical attendance to be 72% versus 42% in those to whom SMS text messaging reminders were sent as compared with the control group with no intervention [14]. A meta-analysis and systematic review also found that SMS text messaging reminders serve as a simple and efficient method of improving health service delivery, as well as conferring health benefits to the patients who receive the reminders [15].

In recent years, mobile phone usage has boomed in Pakistan, with 140 million mobile phone subscribers and 237.58 billion person-to-person SMS text messages generated in 2011 [16,17]. A potential limitation to the use SMS text messaging based interventions is the level of literacy. However, there have been mixed inputs related to preference of phones calls as compared with SMS text messages in populations of low literacy and resource-constrained settings [18,19]. Mobile phone text messages in local languages or local language written in English in combination with phone call can further reduce this gap [20]. While one SMS text message has a maximum allowance of 160 characters only, this limit might help keep the messages short and easy to understand for a low literacy population [21].

To improve patient’s clinic attendance and decrease “no show,” the Aga Khan University outpatient clinic sends automated two-way SMS text messages or telephonic calls as appointment reminders. The cost of the SMS text messages and the phone calls is borne by the Aga Khan University Hospital (AKUH). However, the reply cost of the SMS text message is borne by the patient, in which an SMS text message is sent to the patient in English with a reply option of Yes or No for attending the clinic appointment. In 2016, around 70,000 appointments were given for pediatrics consultancy clinic, out of which 21,150 (30.21%) appointments resulted in “no show,” despite the vigorous policies followed at the consultant clinic. Therefore, our aim is to evaluate the efficacy of the SMS text messaging and calls–based reminder system and further explore how to improve the attendance at the pediatric outpatient clinics at Aga Khan University Hospital, Karachi, Pakistan.

## Methods

### Study Setting

This study will be conducted at the pediatric consulting clinics of the Aga Khan University Hospital, Karachi, Pakistan. AKUH is a 560-bed tertiary care hospital that is accredited by the Joint Commission International (JCI) and is located in Karachi, the largest city of Pakistan with a population of over 14.9 million [22]. The Department of Pediatrics and Child health is one the biggest service providing facility across Pakistan with over 120-bed capacity. Along with general pediatrics, it provides a number of subspecialty services, including, Pediatric Neurology, Neonatology, Cardiology, Intensive care, Infectious diseases, Metabolic, Genetics, Endocrinology, Nephrology, Pediatric Surgery, and Rheumatology. The department provides extensive outpatient services in each of these specialties in the form of morning, afternoon, and evening clinics. Patient turnover last year (2016) in outpatient Pediatrics Clinics was 98,074.

### Study Design

The study uses a mixed-method design which consists of 3 components (see Figure 1).

**Figure 1 figure1:**
[figure not shown]
The mixed-method design of the study, which consists of three components: retrospective data, qualitative data, and quantitative data. SMS: short message service; FGD: focus group discussion; IDI: in-depth interview.

#### Retrospective Component A

A historical cohort data of pediatrics consultant clinic will be evaluated to determine the efficacy of phone-based reminders (SMS text messaging and call service) on patient’s clinic attendance during period of January to June 2017 (N=58,517). Data regarding patient appointments, SMS text messaging and phone call reminders, and actual patient attendance at the clinic will be collected. The primary objective is to evaluate whether SMS text messages and phone calls can improve patients’ appointment attendance at pediatric consulting clinic. The secondary objective is to compare the effect of SMS text messaging versus phone calls on improving clinic attendance.

The primary objective is to evaluate whether SMS text messages and phone calls can improve patients’ appointment attendance at outpatient clinic. For reporting characteristics of patients attending outpatient clinics of AKUH, continuous variables will be expressed as mean and standard deviation or median and interquartile range as appropriate. Categorical variables will be presented as proportions. Chi-square test or Fisher exact test (if expected frequency of each cell is <5) will be employed to determine whether there is a statistical difference in outpatient clinic attendance in group (1) receiving SMS text message, (2) receiving phone call, and (3) receiving both, SMS text message and phone call.

To study the association of patient-level characteristics with nonappearance at the clinic, a multivariable logistic regression will be applied to identify the predictors of patient’s attendance taking into consideration the mode of reminders (SMS text messaging, phone call, or both) and other characteristics that can be adjusted in the model. All statistical tests will be performed on Statistical Package for Social Sciences for Windows version 19 (IBM Corporation). A *P* value of .05 or less will be considered significant.

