## Results

Results of this study will be disseminated to the government and private hospitals/clinics’ pediatric and public health communities in Pakistan through scientific meetings and also submitted for publication in a peer-reviewed journal with an international public health audience. The results of this study may advise other organizations or countries to adopt this strategy to improve patient’s attendance and decrease “no show” through sending automated two-way SMS text message along with the telephonic calls as appointment reminders.

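### Component A ties attendance by reminder group only to an unadjusted test, and the planned adjusted model is not named as the analysis of either causal objective

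*Protocol article*

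**What the plan says.** All of the analysis text is in the protocol article, Methods, Retrospective Component A.

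- **Design and aim.** "A historical cohort data of pediatrics consultant clinic will be evaluated to determine the efficacy of phone-based reminders", using January to June 2017 data with N=58,517.
- **Objectives.** "The primary objective is to evaluate whether SMS text messages and phone calls can improve" attendance; and "The secondary objective is to compare the effect of SMS text messaging versus phone calls on improving clinic attendance". Both ask about an effect.
- **Group comparison.** A chi-square test, or Fisher's exact test for small expected counts, "will be employed to determine whether there is a statistical difference in outpatient clinic attendance" across three groups: SMS, phone call, and both reminders. No group without a reminder is listed. The paragraph holding this test opens by restating the primary objective.
- **Regression.** The next paragraph plans a multivariable logistic regression. Its stated purpose is to relate patient-level characteristics to non-attendance and to identify predictors of attendance. It takes reminder mode into account together with "other characteristics that can be adjusted in the model".

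Elsewhere, the Introduction describes a routine service that sends SMS or makes calls, and gives no rule for which appointment gets which reminder. The Results section says the findings may lead others to adopt "sending automated two-way SMS text message along with the telephonic calls as appointment reminders". Discussion, Limitations covers the single private institution, socioeconomic selection and the estimation of barriers. It does not mention confounding between reminder groups.

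**The concern.** Reminder mode was not assigned at random, and nothing in the article makes the SMS, call and both groups exchangeable. If the groups differ in anything that also predicts attendance, such as specialty, booking lead time or attendance history, a crude comparison mixes that difference with any effect of the reminder. The bias can go either way.

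The article does plan a model that could reduce this bias, but gives that model a different job. The group comparison is attached to the unadjusted test. If the crude and adjusted results disagree, the text gives no reason to prefer the adjusted one. A predictor search also need not contain the variables that determine reminder mode, and those are the ones that control of confounding requires.

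Sample size makes this worse in practice. The Strengths section presents the volume of data as an advantage, but volume narrows the confidence interval around a biased difference without removing the bias. At stake is whether a case-mix difference is reported as the efficacy of a reminder mode.

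**Working it through.** **Inputs from the protocol article**

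- N = 58,517 (Retrospective Component A). The unit is taken to be the appointment, and appointments are treated as independent.
- 2016 no-show: 21,150 of about 70,000 (Introduction). Check: 21,150 / 70,000 = 0.3021, which agrees with the stated 30.21%. Attendance p = 1 − 0.3021 = 0.6979 and p(1 − p) = 0.2108.
- Significance level 0.05, taken as two-sided.

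**Assumed, because the article gives neither group sizes nor case mix**

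- Group shares: equal thirds, or 80/10/10.
- One binary confounder, with prevalence 50% in one group (the 80% group in the unequal split), 50% + δ/2 in the second and 50% − δ/2 in the third. δ runs from 5 to 30 points.
- The confounder shifts attendance by RD = 5 to 20 points.
- Reminder mode has no effect at all.

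**Step 1: what N can detect.** The smallest pairwise difference detectable with 90% power at 70% attendance is 1.5 points with equal thirds, 2.0 points for 10% against 80% of appointments, and 2.8 points for 5% against 90%. Small differences of any origin will therefore reach significance.

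**Step 2: spurious gap.** The largest crude difference between groups is g = δ × RD. The smallest is 0.05 × 0.05 = 0.0025 (0.25 points). The largest is 0.30 × 0.20 = 0.06 (6 points).

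**Step 3: false-positive rate of the crude three-group chi-square (2 df).** The noncentrality is λ = Σ n_k (p_k − p)² / [p(1 − p)]. Only the two outer groups deviate, each by g/2, so λ = 2 n (g/2)² / 0.2108, where n is the size of each outer group.

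Worked example with δ = 20 points, RD = 10 points, g = 0.02:

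- Equal thirds, n = 58,517/3 = 19,505.7: λ = 2 × 19,505.7 × 0.0001 / 0.2108 = 18.5; rejection probability 97.8%.
- 80/10/10, n = 5,851.7: λ = 2 × 5,851.7 × 0.0001 / 0.2108 = 5.55; rejection probability 54.9%.

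| Spurious gap (points) | Rejects, equal thirds | Rejects, 80/10/10 |
|---|---|---|
| 0.25 | 7% | 6% |
| 0.5 | 15% | 8% |
| 1 | 47% | 17% |
| 1.5 | 83% | 33% |
| 2 | 98% | 55% |
| 3 | about 100% | 90% |
| 4 | about 100% | 99% |
| 6 | about 100% | about 100% |

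**Step 4: does adjustment help?** A simulation of 400 studies used N = 58,517, equal thirds, confounder prevalence 50/60/40% and RD = 10 points, again with no reminder effect. The crude chi-square was significant in 98% of runs. A likelihood-ratio test for mode in a logistic model containing the confounder was significant in 4.5%, against a nominal 5%. This benefit exists only if the confounder is recorded and entered in the model.

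**The case against.** The strongest reply is that adjustment is already planned. The regression follows directly after the chi-square, contains reminder mode and will yield an adjusted odds ratio for it. This stands: the chi-square is not the only analysis of reminder mode, and the article does not label it the efficacy test. A reader might infer that the crude test is the declared test of efficacy and that confounding is ignored altogether, but the text does not support that. What remains is that neither analysis is named for the objectives, and the adjusted one is given a different purpose.

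A second reply is that a condensed article may leave the covariate list and the exact definition of exposure to the full protocol or SAP. This also stands, and their absence is not the point here. The point is the role that the article itself gives to each analysis.

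Third, the mechanisms of confounding are not documented. A reader might infer that receiving a call means answering it, or that both reminders were used when an SMS went unanswered or risk was judged higher. The article says neither. A reader might also infer that the wider adoption mentioned in the Results section rests on the chi-square; that sentence concerns dissemination and names no analysis.

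Finally, the size of the bias rests on assumed case mix. That is true, and it is why a range is given.

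**Conclusion.** The concern holds in limited form. In a non-randomised cohort with causal objectives, the group comparison is tied to an unadjusted test, while the model that could reduce confounding is presented as a predictor search. Confounding is not among the stated limitations.

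The size cannot be estimated from the article. Under the assumed ranges, the crude test's false-positive rate lies anywhere from close to nominal to near certainty. The low end matters too: with small imbalances, or with unequal groups and a weak confounder, little harm is done. The calculation assumes one binary confounder, independent appointments and no true reminder effect. It shows what could happen and does not show that the groups in fact differ.

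Adjustment has its own limit. All three groups received a reminder, so even a well-adjusted mode comparison addresses the secondary objective and does not show whether a reminder is better than none.

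**What to change.** 1. Name the adjusted odds ratio for reminder mode, from the regression already planned, as the main analysis of the mode comparison. Label the chi-square or Fisher test descriptive.
2. Adjust for determinants of reminder mode as far as the appointment system records them, for example specialty or clinic session, month, booking lead time and previous no-show. The article mentions only appointment, reminder and attendance data, so availability has to be checked.
3. Group appointments by reminder sent or attempted according to the log, so that membership does not depend on the family's response.
4. State residual confounding as a limitation and report Component A results as association instead of efficacy.
5. Say that comparing SMS, call and both does not show the effect of a reminder against none.

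The cost is some extra data extraction and a more cautious conclusion. No new participants and no new model are needed.

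### The unit of the 58,517 records is not defined; if they are appointments, the planned tests ignore correlation within child and clinic, and standard errors for patient-level and clinic-level factors are likely too small

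*Protocol article*

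**What the plan says.** All of the analysis text is in the protocol article, Methods, Retrospective Component A.

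- **Size and period:** attendance is studied "during period of January to June 2017 (N=58,517". The article does not say what this number counts.
- **Data:** "Data regarding patient appointments, SMS text messaging and phone call reminders, and actual patient attendance at the clinic will be collected".
- **Group comparison:** "Chi-square test or Fisher exact test (if expected frequency of each cell is <5) will be employed" to compare attendance across SMS only, call only, and both.
- **Model:** its purpose is stated as "To study the association of patient-level characteristics with nonappearance at the clinic", and for this "a multivariable logistic regression will be applied to identify the predictors of" attendance, taking reminder mode and other characteristics into account.
- **Threshold:** a P "value of .05 or less will be considered significant". Sidedness is not given.

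The section names no random effect, GEE, cluster-robust variance or rule of one appointment per child. Study Setting describes general pediatrics and 11 named subspecialties, with "extensive outpatient services in each of these specialties in the form of morning, afternoon, and evening clinics".

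**The concern.** Pearson chi-square, Fisher exact and ordinary logistic regression all take each record as independent. Reminders and attendance belong to appointments, so an extract of these data most naturally has one row per appointment. A child followed in neurology, cardiology or nephrology may then supply several rows in six months. Families that miss one visit are likely to miss others, and no-show habits may differ between clinics.

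The model is meant to find predictors among patient-level characteristics. These are constant, or nearly so, across one child's appointments, and that is the case in which ignoring the correlation makes standard errors too small. Confidence intervals would be too narrow, and some chance associations would be reported as predictors of attendance. Children with many visits would also carry more weight than the plan acknowledges. The article intends its findings to support recommendations on reminder services, so the predictors will be used.

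**Working it through.** **1. What does N count?** N=58,517 has no derivation to reproduce; it is a count of existing records. The Introduction gives a related rate for 2016: 21,150/70,000 = 0.3021, which matches the stated 30.21% and is counted per appointment. Against the article's own volumes:

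- 58,517/70,000 = 0.84 of the approximate number of appointments given in all of 2016 (Introduction).
- 58,517/98,074 = 0.60 of the 2016 outpatient turnover (Study Setting).
- 2 × 58,517 = 117,034 on an annual basis, which is above both figures.

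Six months of records are thus on the scale of total clinic traffic, which favours appointments over distinct children. The comparison does not prove it, because the annualised figure agrees with neither volume.

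**2. Formulas.** For a single contrast, with m records per cluster, ICC_y for the outcome and ICC_x for the exposure or covariate:

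- Design effect DE = 1 + (m − 1) × ICC_y × ICC_x
- Effective N = 58,517/DE
- Type I error = 2 × (1 − Φ(1.96/√DE)), two-sided .05 assumed

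The document gives no m, ICC or number of clinicians. All values below are assumptions.

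**3. Patient-level covariate, constant within child (ICC_x = 1).**

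| m | ICC_y | DE | SE understated by | Effective N | Type I error |
|---|---|---|---|---|---|
| 2 | 0.1 | 1 + 1 × 0.1 = 1.10 | 1.05 | 53,197 | 0.062 |
| 2 | 0.3 | 1 + 1 × 0.3 = 1.30 | 1.14 | 45,013 | 0.086 |
| 4 | 0.3 | 1 + 3 × 0.3 = 1.90 | 1.38 | 30,798 | 0.155 |

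With one appointment per child, DE = 1 and there is no child-level problem.

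**4. Reminder mode, which may vary within child (m = 2, ICC_y = 0.3).**

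| How mode varies | ICC_x | DE | Type I error |
|---|---|---|---|
| Balanced within each child | −1 | 0.70 | 0.019 |
| Unrelated to child | 0 | 1.00 | 0.050 |
| Partly constant within child | 0.5 | 1.15 | 0.068 |
| Constant within child | 1 | 1.30 | 0.086 |

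The direction of the error therefore depends on how reminders were allocated, which the article does not describe.

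**5. Clinician level.** Assume 60 clinicians, so m = 58,517/60 ≈ 975, with ICC_y = 0.01.

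- Mode fixed by clinician (ICC_x = 1): DE = 1 + 974.3 × 0.01 = 10.7, type I error 0.55 (simulation of 1,500 runs: 0.57).
- Mode partly clustered (ICC_x = 0.2): DE = 2.95, type I error 0.25 (simulation: 0.26).
- Mode unrelated to clinician: DE = 1.0, type I error 0.05 (simulation: 0.044).

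Assume instead 200 appointments per clinician, which implies 58,517/200 ≈ 293 clinicians. With mode fixed by clinician and the same ICC_y, DE = 1 + 199 × 0.01 = 2.99 and the type I error is 0.257. The answer depends heavily on a number that the article does not give.

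**6. Practical scale.** With equal thirds and a no-show rate of 30.21%, the naive standard error of a difference between two modes is √(0.3021 × 0.6979 × 2/(58,517/3)) = 0.00465, a 95% half-width of 0.91 percentage points. At a design effect of 1.9 the half-width is 0.91 × 1.38 ≈ 1.26 points.

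**The case against.** Five points can be made for the plan.

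- **Repeat visits are inferred.** No section says that children return within the window, and the clinic-session description in Study Setting is not evidence of it. This stands, and the point is conditional for that reason. If N did count children, however, the article would need a rule for choosing or summarising their appointments, and it gives none.
- **A reader might infer that all standard errors and P values are too small.** The documents do not support that. For reminder mode, the subject of the primary and secondary objectives, the error vanishes when mode is unrelated to cluster and reverses when mode is balanced within child. Only patient-level and clinic-level factors have a likely direction.
- **A reader might take the large clinician-level figures as the expected size.** They rest on an assumed number of clinicians, an assumed ICC and reminder mode following clinician. None of these is in the article.
- **A condensed article may leave variance estimation to a fuller document.** This stands in part: a logistic regression can carry a robust variance, and adjustment for other characteristics could include specialty. The Pearson or Fisher test, by contrast, is fixed here by name, and in its standard form it has no such option.
- **With this many records, the practical effect may be small.** At child level, a half-width of 0.91 against 1.26 points seldom changes a conclusion of practical importance, and confounding in who receives which reminder is probably the larger threat. This lowers the severity but does not make the named tests valid.

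**Conclusion.** The point holds in conditional form and is moderate; the text is wrong as written. The unit of analysis is undefined. On the most plausible reading, appointments, the named methods ignore correlation within child and within clinic or clinician. Standard errors for the patient-level predictors that the model is meant to identify, and for clinic-level factors, are then likely too small. For reminder mode the direction is open.

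The document does not allow the size to be computed. The illustrative range of 6% to 16% type I error (design effect 1.1 to 1.9) rests on 2 to 4 appointments per child, an ICC of 0.1 to 0.3, a covariate constant within child and a two-sided test. Clinician-level effects could be larger if reminder mode follows clinician, or absent if it does not.

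**What to change.** In Retrospective Component A:

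1. State that the appointment is the unit of analysis and that 58,517 counts appointments. If it counts children, say so and give the rule that selects or summarises each child's appointments.
2. Fit the attendance models by GEE, or by logistic regression with cluster-robust standard errors, clustered on the child. Include clinic or specialty as a covariate, or clinician as a further cluster level.
3. Take the P value for the comparison of reminder groups from that model in place of the Pearson or Fisher test.
4. Add a sensitivity analysis on each child's first appointment in the window. This removes child-level correlation only; appointments within a clinic or clinician remain correlated.

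The cost is analysis work and wording, with somewhat wider confidence intervals for most factors. The extract must carry a child identifier, plus clinic or clinician; the article does not say whether it does, so this should be confirmed before the data are pulled.
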